### Randomisation and blinding

Participants are randomly assigned to one of the two groups at a 1:1 ratio using a minimisation algorithm. The minimisation factors are the centre, the type of SCD, and the occurrence of VOC during the year before inclusion. Allocation is done using a central randomisation system (Ennov Clinical, version 7.5.710.4, San Francisco, CA, USA). At each centre, a clinical research associate delegated by the investigator and who is trained in good clinical practice (GCP) logs into the central randomisation system and inputs patient information; a random number and group assignment are then immediately given by the system. Because DREPADO is an open-label trial, the clinical research associate directly informs the patient-caregiver dyad of the arm to which they are assigned (Arm A or B).

### Study scheme

The Standard Protocol Items: Recommendation for Interventional Trials (SPIRIT) flow diagram is presented in Fig. 1 and the detailed study scheme in Fig. 2.

**Fig. 1 Fig1:**
[figure not shown]
SPIRIT flow diagram of the DREPADO trial

**Fig. 2 Fig2:**
[figure not shown]
Detailed study scheme of the DREPADO trial

#### Arm A – control group

Patients and caregivers randomised to the control group receive the standard care management used in the study centre, including a joint consultation with a paediatrician and an internist/haematologist between the age of 16 and 18 years, and a visit to the adult department of care.

#### Arm B – intervention group

In addition to standard management, patients and caregivers randomised to the intervention group benefit from the SCD paediatric-adult transition programme. Based on the biopsychosocial approach, this consists of three structured axes, the objectives of which and practical details are summarised in Table 1.

**Table 1 Tab1:** The three axes of paediatric-adult transition programme

Axes	Public	Objectives	Contents	Practical details	Providers
Educative	Patient and caregiver dyad	Providing self-care knowledge and skills related to SCD and therapeutics	Knowledge and coping skills, with patient needs assessment	Face to face At patients’ home 3 sessions of 2 h	One healthcare professional, trained in patient education and in SCD
Psychological	Individual patient i	Helping empower patients in relation to pain management and emotions	Knowledge and coping skills, with patient needs assessment	Face to face At hospital 6 sessions of 1.5 h	One healthcare professional, trained in therapeutic hypnosis and in SCD
Social	Group of 4 to 8 patients	Facilitating the relationship with oneself, others, and care	Coping skills	Face toface At ‘neutral place’ as association patient place 2 sessions of 2 h	One healthcare professional and one expert patient, both trained in patient education and in SCD

*h* hour*, SCD* sickle cell disease

The modifiable factors are used as coping skills during the educative, the psychological, and the social axis. The objective of the educative axis is to provide knowledge and coping skills related to self-care management. It is conducted at home with the patient and his/her parent by a healthcare professional trained in patient education. The objective of the psychological axis is to help empower patients in relation to pain management and emotions. It is conducted at hospital with only the patient by a healthcare professional trained in therapeutic hypnosis. The objective of the social axis is to facilitate the relationship to oneself, others, and care. It is conducted in a ‘neutral place’ (not at home and not at the hospital) with a group of patients by a healthcare professional trained in patient education and an expert adult patient also trained in patient education.

### Outcome measurements

The primary outcome is number of hospital admissions and emergencies in the index hospital for complications (i.e*.* VOC, ACS, and/or stroke) in the 2 years after T-transfer.

To evaluate the biopsychosocial approach, the secondary outcomes include bioclinical, psychological, and social factors, measured at T-inclusion, T-transfer, T-12, and/or T-24, collected from patients and/or parents. With regard to the indirect bioclinical factors, the use of care is evaluated by the incidence of emergency visits and medical consultations at T-24. Medication adherence is also measured at T-inclusion, T-transfer date, T-12, and T-24 by adapted Medication Intake Survey-Asthma (MIS-A) [17] adapted for SCD and Medication Adherence Report Scale (MARS) [18]. Psychological factors, such as pain perception, and social factors, such as school absenteeism is measured by self-declaration. Quality of life is evaluated using the brief World Health Organisation Quality of Life questionnaire (WHOQOL-Brief), and skills are measured by questionnaires, such as the health literacy using the European Health Literacy Questionnaire (HLS-EU-Q16) [19], self-efficacy feeling using the Self Efficacy Specific Instrument – Sickle Cell Disease (SCD-SES) [20]; these are measured at the T-inclusion, T-transfer, T-12, and T-24. All the data sources are presented in Table 2.

**Table 2 Tab2:** Data collection plan

Outcomes		Time point				Population		Data sources
		T-inclusion	T-transfer	T-12	T-24	Patient	Parent	
Use of care	Hospitalisations for VOC, ACS, stroke		X		X	X		Medical records
	Emergency visits, medical consultations, imaging exams		X		X	X		Medical records
Medication adherence		X	X	X	X	X		2 questionnaires (MARS and adapted-MIS-A)
School absenteeism			X		X	X	X	Auto declaration
Quality of life		X	X		X	X		26-item questionnaire (WHOQOL-Brief)
Health literacy		X	X		X	X		16-item questionnaire (HLS-EU-Q16)
Disease and therapeutic knowledge		X	X		X	X	X	36-item questionnaire
Patient activation		X	X		X	X		13-item questionnaire
Sense of self-efficacy						X		9-item questionnaire (SCD-SES)
Transition preparation		X	X		X	X		20-item questionnaire (TRAQ)
Pain perceptions	At home			X	X	X		Auto declaration (book)
	Intensity during hospitalisations		X		X	X		Medical records

*ACS* acute chest syndrome, *HLS-EU-Q16* European Health Literacy Questionnaire, *MARS* Medication Adherence Report Scale, *adapted-MIS-A* Medication Intake Survey-Asthma, *SCD-SES* Self-Efficacy Specific instrument – Sickle Cell Disease, T*RAQ* Transition Readiness Assessment Questionnaire, *VOC* vaso-occlusive crisis, *WHOQOL-Brief* World Health Organization Quality of Life brief questionnaire

At the end of the study, the lived experience of a sample of patients, parents, and contributors is evaluated. The cost-effectiveness and the implementation of the transition programme are also secondary outcomes.

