## Background

Sickle cell disease (SCD) is a chronic, genetic disease, widespread both around the world and in France. After diagnosis, patients with SCD require medical follow-ups, which are essential to prevent complications. The most frequent complications are vaso-occlusive crises (VOC; which are painful), acute chest syndrome (ACS), and stroke. Thanks to advancements in medical care, a majority of SCD patients worldwide live beyond 18 years of age [1], and therefore, patients initially followed in paediatric departments are then transferred to adult departments.

For patients with chronic disease such as SCD, this paediatric-adult care transition is a period with an increased risk of discontinuity of care [2, 3]. During this period, adherence to medication is sub-optimal [1, 4] and the rate of missed clinical appointments is high [5]. Furthermore, the highest morbidity and mortality is observed between 17 and 18 years of age [6], and young adults frequently use acute care (emergency care and hospitalisations) after paediatric-adult transition [7].

During the paediatric-adult transition, the patient will have to manage new interlocutors and places of care, as well as a different organisation of this. An important aspect to improve the health status of patients is, therefore, to involve both paediatric and adult departments of care in the transition [3]. In addition, the patient will have to manage personal issues related to the period of adolescence [8]: a period of psychological upheaval and adaptation of family roles [9]. To assess the needs of patients with SCD during this transition period, a qualitative study was conducted in Lyon (France). Parents, as well as adolescent and adult patients with SCD, were individually interviewed about it. Results revealed individual and also family needs that concerned knowledge of the disease, coping skills, therapeutics, and psychosocial aspects [10].

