## Methods/Design

### The aim, design, and setting of the study

The DREPADO RCT seeks to assess the impact of a paediatric-adult transition programme. This trial is an interventional study. It is an open-label, individual, multicentre RCT comparing a control group (Arm A) to an interventional group with a paediatric-adult transition SCD programme based on the biopsychosocial approach (Arm B).

The DREPADO trial is a French national RCT including centres specialised in SCD patient care, involved in the SCD health network (*Maladie Chronique du Globule Rouge et des autres maladies de l’érythropoïèse* Filière - MCGRE) accredited by the French Ministry of Health and motivated to participate in this study. The coordinating centre is Lyon University Hospital, and five other centres will participate (Créteil, APHP Kremlin-Bicêtre, Martinique, APHP Necker, Pontoise).

The follow-up period is a maximum of 4 years for each patient. Outcomes is assessed at baseline (T-inclusion), at transfer date – which corresponds to the first consultation in the adult department of care (T-transfer), 12 months after transfer (T-12), and 24 months after transfer (T-24).

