#### Inclusion criteria

Patients are included if they fulfil the following conditions: having the SS, SC, or Sβ form of SCD; aged between 16 and 17 years; orally agreeing to participate. The caregiver is included if they fulfil the following conditions: parent or legal guardian of the patient; aged more than 18 years; having provided a signed written consent for him/herself and for the patient.

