### Statistical analysis plan

Demographics and other characteristics are reported descriptively and according to treatment group. Means and standard deviation (SD), or medians and ranges when appropriate are calculated for continuous variables. Categorical variables will be presented using numbers and percentages.

The crude rate of hospitalisations due to complications will be calculated by dividing the total number of hospitalisations due to VOC, ACS, and stroke occurring after transfer by the total duration of follow-up of all patients in each group. The treatment effect will be assessed using a multivariable Poisson regression model with the study group as a factor, adjusting for minimisation factors and relevant patient characteristics and the length of follow-up as the offset. Results will be expressed as a rate ratio with 95% confidence interval. A negative binomial model will be fitted if data are over-dispersed. The same analyses will be performed for the association between intervention and other secondary outcomes.

Analysis of covariance (ANCOVA) will be used to evaluate the intervention effect at T-24 on all the secondary outcomes evaluated by questionnaires. Scores will be computed and depicted at each assessment by following the scoring procedures for each questionnaire. Each ANCOVA will include the baseline measure (T-inclusion) and minimisation factors as covariates. Changes over time for each score will be also assessed using generalized estimation equation analyses to test the effect of group, time, and the interaction group time after controlling for minimisation factors and relevant patient characteristics.

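### The primary window opens only at a first adult consultation after randomisation, so a randomised patient who never attends has no primary outcome and the arms are compared among attenders only

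*Protocol article*

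**What the plan says.** Under Inclusion criteria, patients enter when "aged between 16 and 17 years; orally agreeing to participate". They are randomised at that stage, while still in paediatric care.

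Under Outcome measurements, the primary outcome is the number of index-hospital admissions and emergencies for complications, "VOC, ACS, and/or stroke) in the 2 years after T-transfer". The section on aim, design and setting fixes T-transfer as the transfer date, "which corresponds to the first consultation in the adult department of care (T-transfer"), and T-12 and T-24 are counted from it.

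The Statistical analysis plan section forms the crude rate from events due to VOC, ACS and "stroke occurring after transfer by the total duration of follow-up of all patients in each group". It then fits a Poisson model, or a negative binomial model if data are over-dispersed, with "the length of follow-up as the offset".

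No section gives a start date for a patient with no adult consultation. Withdrawal and discontinuation covers only participants who cannot be reached after four calls. The 10% inflation under Sample size names missing data, withdrawal and loss to follow-up.

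**The concern.** Time zero of the primary outcome is something the patient does after randomisation. If the arms differ in who reaches it, the analysed groups are no longer those that were randomised.

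The document gives reason to expect that they might differ. The Background motivates the trial by saying that for these patients "this paediatric-adult care transition is a period with an increased risk of discontinuity of care", and notes frequent missed appointments. Table 1 gives the social axis the aim of a better relationship with care. The Discussion says the programme starts in the paediatric department and continues in the adult one. The trial is open-label, so patients and staff know the arm.

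The design targets a reduction of only 15%, so even modest selection into the analysed set could move the estimate by an amount that matters.

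**Working it through.** **The plan's own figure.** Inputs from Sample size: 3.5 events per patient-year, rate ratio 0.85, 80% power, two-sided 5%, 10% inflation. Over 2 years the means are 7.0 and 5.95. Using the log rate ratio with the null variance under H0:

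n = (1.96·√(2/7) + 0.8416·√(1/7 + 1/5.95))² / (ln 0.85)² = 87.1, so 88 per arm; 88/0.90 gives 98 per arm, 196 in total.

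The stated 196 is reproduced. It contains no allowance specific to non-transfer.

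**What happens to a patient who never attends.**

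- (a) Natural reading: follow-up in the model is post-transfer time, matching the outcome definition. Exposure is 0, the log of the offset is undefined, and the patient leaves the model.
- (b) Less natural reading: follow-up of all patients runs from inclusion. The patient then adds time to the denominator but can have no countable event.

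**Illustration under (a).** None of the following inputs is in the document; they are assumptions. A share qA of controls and qB of programme patients never transfer. Patients who transfer only because of the programme have h times the usual event rate. Then

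apparent ratio = true ratio × [(1 − qA) + (qA − qB)·h] / (1 − qB).

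With qA = 0.20 and qB = 0.10 the multiplier is (0.80 + 0.10h)/0.90:

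| h | Multiplier | True 1.00 appears as | True 0.85 appears as |
|---|---|---|---|
| 0.5 | 0.85/0.90 | 0.944 | 0.803 |
| 1 | 0.90/0.90 | 1.000 | 0.850 |
| 1.5 | 0.95/0.90 | 1.056 | 0.897 |
| 2 | 1.00/0.90 | 1.111 | 0.944 |

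With qA = 0.10 and qB = 0.05 the multiplier is (0.90 + 0.05h)/0.95, and 0.85 appears as 0.828, 0.850, 0.872 or 0.895. With qA = qB and comparable patients the multiplier is 1.

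**Power under (a), 20% v 10%, 98 randomised per arm, pure Poisson variance.** Control events are 98 × 0.80 × 7 = 548.8. Programme events are 98 × 7 × 0.85 × (0.80 + 0.10h). Power = Φ(|ln apparent ratio| / √(1/events A + 1/events B) − 1.96).

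- All 98 per arm evaluable, no selection: 0.82. With the 88 the plan expects: 0.78.
- h = 1: 524.8 programme events, power 0.76. This is loss of patients alone, without bias.
- h = 1.5: 553.9 events, power 0.44.
- h = 2: 583.1 events, power 0.16.
- h = 0.5: 495.6 events, power 0.94, but for an effect that is overstated.

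**Reading (b), for comparison.** If never-transferred patients are credited with the same follow-up time as the others, the multiplier is (0.80 + 0.10h)/0.80. At h = 1 a true 0.85 appears as 0.956 and a true 1.00 as 1.125.

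**The case against.** **Both arms are offered adult care.** Standard care includes a joint consultation and a visit to the adult department (Arm A section), and Arm B receives it too. This may keep non-transfer low, and it makes 20% v 10% a strong assumption: 20% in one arm is twice the whole planned allowance. This stands as a limit on size. It does not remove the gap, because the text does not say that this visit is the first consultation or that it always takes place.

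**Attendance is not a named target.** A reader might infer that attending the first adult consultation is what the programme sets out to change. No axis in Table 1 says so; the link is an inference from the rationale. The comparison is exposed if the programme can affect attendance, whether or not that is its aim.

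**Direction.** A reader might infer that the bias works against the programme, or that the sickest patients are the ones lost. The documents support neither. Patients with many index-hospital admissions could be the likeliest to reach adult care, and at h = 0.5 the bias under (a) favours the programme.

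**Scoring as event-free.** A reader might take the crude-rate sentence to mean that non-attenders count as successes. That requires follow-up to start at inclusion, which sits badly with an outcome window starting at T-transfer. It also needs an assumption about how much time such patients contribute.

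**Leave it to the SAP.** Analysis sets are normally defined there, and the anchor matches the stated question about outcomes after transfer. But the protocol itself fixes the outcome window. A SAP cannot give a never-transferred patient a window without changing that definition.

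**Conclusion.** The point holds as a flaw in a stated definition. Followed as written, the plan leaves a randomised patient who never attends an adult consultation without a primary outcome, and compares the arms among attenders.

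The size and direction are unknown. On the assumed 20% v 10% non-transfer, a true 0.85 appears as anything from about 0.80 to 0.94 as the relative rate of the extra attenders goes from 0.5 to 2. On 10% v 5% the range is about 0.83 to 0.90. There is no distortion if non-transfer is equal and the patients are comparable, or if the extra attenders have the usual rate. The power figures assume pure Poisson variance, whereas the plan allows for over-dispersion; that would change the power but not the bias.

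The documents do not show that a working programme would look null or harmful, and that should not be claimed.

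**What to change.** Give every randomised patient a primary window:

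1. Keep T-transfer as the start where it occurs. For a patient with no adult consultation, start the 2 years at a date that does not depend on attendance, for example the 18th birthday. With entry from the 16th birthday, that window closes at the 20th birthday, at most 4 years after inclusion. This fits the stated limit: "The follow-up period is a maximum of 4 years for each patient".
2. Count index-hospital events in paediatric or adult departments. Table 2 already takes hospitalisations and emergency visits from medical records.
3. Analyse all randomised patients for whom consent allows.
4. Report the share transferred and the time to transfer by arm, next to the primary result.
5. Add a sensitivity analysis that starts everyone's window at the 18th birthday. The fallback in step 1 still lets the start date depend on attendance, so it does not restore full protection by itself.

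Moving the primary window to the 18th birthday for everyone would be cleaner as a randomised comparison, but it changes the stated question about outcomes after transfer, so it is better kept as the sensitivity analysis.

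The cost is mainly wording, using dates and records that should already be at hand. The sample size stays at 196 provided 3.5 events per year also applies to the fallback window. There are three downsides. Part of the window may fall in paediatric care. Patients must give their own consent at 18, and records of those who do not may be unavailable. Events treated outside the index hospital remain uncounted.

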## Discussion

Owing to the risk of discontinuity of care in chronic disease patients, it is essential to improve the paediatric-adult care transition. The DREPADO project is the first RCT designed to assess the impact of a paediatric-adult transition programme. The latter is based on the available literature [3] and on a recent previous qualitative study [10]. In accordance with this, it involves both paediatric and adult departments of care by starting the intervention in a paediatric department and continuing it in adult department of care. In addition, the qualitative study found that the needs of parents and patients were biopsychosocial, both individual and familial [10]. Added to that, the modifiable factors of the SMART [11, 12] were included in the three axes of the programme, to become patients’ coping skills. Furthermore, because the previous qualitative study [10] found the need for an integrated caregiver programme, the educative axis involves both the patient and their parent. This axis is conducted at home as this is patient’s environment as opposed to the hospital, which is the environment of care [21].

The primary outcome is bioclinical, which is more objective than complications measured in terms of pain. Secondary outcomes consider aspects related to the patient using a whole system approach, such as quality of life, but also include coping skills such as sense of self-efficacy, health literacy, and disease knowledge. In addition, as the transition of care is stressful and generally experienced by both patients and their parents, lived experiences of the proposed care transition programme are also evaluated.

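### School absenteeism has no T-inclusion value: the arm comparison stays valid, but precision, a balance check and any before/after reading are given up for want of one short item

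*Protocol article*

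**What the plan says.** In the protocol article, the Outcome measurements section gives absenteeism as an example of a social factor: "social factors, such as school absenteeism is measured by self-declaration". That sentence states no time point. Table 2 supplies it: "School absenteeism X X X X Auto declaration". In the table's columns, the first two marks are T-transfer and T-24 and the other two are patient and parent. The T-inclusion and T-12 cells are empty.

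The general schedule in the same section is permissive: secondary outcomes are "measured at T-inclusion, T-transfer, T-12, and/or T-24, collected from patients and/or parents". The section on aim, design and setting defines baseline as T-inclusion: "Outcomes is assessed at baseline (T-inclusion), at transfer date".

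The Statistical analysis plan section has two rules for secondary outcomes:

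- ANCOVA estimates "the intervention effect at T-24 on all the secondary outcomes evaluated by questionnaires", and "Each ANCOVA will include the baseline measure (T-inclusion) and minimisation factors as covariates".
- For the rest, after describing the Poisson or negative binomial model, it says "The same analyses will be performed for the association between intervention and other secondary outcomes".

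On the timing of the programme, the Discussion describes "starting the intervention in a paediatric department and continuing it in adult department of care".

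**The concern.** Absence before the programme plausibly predicts absence afterwards, so a baseline value would normally be the natural covariate for this outcome. None is collected. The earliest scheduled value, at T-transfer, is post-randomisation and is taken once Arm B has been exposed to the programme. Adjusting for it could remove part of the effect being estimated.

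Three things are at stake for this secondary outcome:

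- the precision of the arm comparison;
- the ability to show whether the arms were alike in absence at entry;
- any statement about change from before the programme.

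An analysis plan can choose among collected covariates, but it cannot supply an item that was never asked. The gap therefore lies in the data collection plan, which the article prints in full for this row.

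**Working it through.** **1. Is there a T-inclusion value anywhere?** Table 2 has none for absenteeism. The sentence in Outcome measurements that lists all four time points concerns quality of life and skills. The general schedule does not promise T-inclusion for every outcome. So no baseline value is planned.

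**2. Could T-transfer serve as baseline?** The article defines baseline as T-inclusion and T-transfer as the first adult consultation. The Discussion places the start of the intervention in the paediatric department, before that consultation. The article states no look-back that would make the T-transfer answer refer to time before the programme. So it cannot.

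**3. Is there a substitute?** The minimisation factors are centre, type of SCD, and VOC in the year before inclusion. None is absence, although prior VOC may be related to it. Hospitalisations and emergency visits also lack a T-inclusion mark, but they come from medical records and can be looked up later. Self-declared absence has no such source in the article.

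**4. Is the inclusion visit able to carry the item?** Table 2 already places medication adherence, quality of life, health literacy, knowledge, patient activation and transition preparation there, and knowledge is collected from the parent as well.

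**5. The plan's only sample-size figure.** The article gives no figure for absenteeism. The 196 concerns the primary outcome. Inputs are a rate of 3.5 per patient-year, 2 years, rate ratio 0.85, 80% power and two-sided 5%. With a Poisson-regression formula:

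N = [1.960 × √4 + 0.842 × √(2 + 2/0.85)]² / (3.5 × 2 × (ln 0.85)²) ≈ 174.2

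This is 88 per arm, 176 in total, and 176 / 0.9 = 195.6, which rounds up to 196. The figure is reproduced, and a baseline item for absenteeism does not enter it.

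**6. Size of the forgone precision.** Let r be the partial correlation between prior and later absence, given the covariates already in the model. The documents give no value, so r is an assumption. Under a linear model:

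- residual variance factor = 1 − r²
- difference detectable at 80% power, with 88 evaluable per arm = (1.960 + 0.842) × √(1 − r²) × √(2/88), in SD units

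| r (assumed) | 1 − r² | Variance reduction | Detectable difference |
|---|---|---|---|
| 0 (no baseline) | 1.00 | 0% | 0.42 SD |
| 0.3 | 0.91 | 9% | 0.40 SD |
| 0.5 | 0.75 | 25% | 0.37 SD |

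Here SD is the residual SD before prior absence is added. Absence is probably a skewed count, and the article's rule for other secondary outcomes points to a Poisson or negative binomial model, so the table is only an approximation.

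**The case against.** The strongest reply is that nothing here is misstated. The general schedule allows an outcome to skip T-inclusion. The T-inclusion covariate rule is confined to questionnaire outcomes, whereas Table 2 lists absenteeism as self-declared and gives it no questionnaire. The schedule also has a logic: hospitalisations, emergency visits, pain intensity in hospital and absenteeism all accrue over a period, and all are marked at T-transfer and T-24 only. All of this stands. A reader might infer an internal contradiction between Table 2 and the ANCOVA rule, but the article does not support that.

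Nor is the comparison biased. Randomisation protects it without a baseline, and the confidence interval already allows for chance imbalance. The count model also adjusts for minimisation factors, including prior-year VOC, and for relevant patient characteristics. A reader might conclude that the absenteeism result would be invalid or wholly unadjusted; neither follows.

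The size is also open to challenge. With a correlation of 0.7, 1 − 0.49 = 0.51, and one could read this as 1 / 0.51 = 1.96, or nearly twice the patients for this outcome. The article does not support that reading. The correlation is assumed, and what matters is what remains after prior VOC, SCD type and centre are in the model. The formula is linear. Follow-up may last up to 4 years from entry at 16 to 17, a long interval over which to assume so strong a correlation.

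Finally, Figures 1 and 2 are not available, and Table 2 has one row (self-efficacy) without any time point although the text gives four, so a typesetting slip is possible. The absenteeism row, however, is filled in, and nothing in the text disagrees with it.

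What survives is narrow: a useful value that only the inclusion visit can supply prospectively is not collected, although the visit could carry it at little cost.

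**Conclusion.** The point holds as a minor, inexpensive improvement to the data collection plan, not as an error or contradiction. School absenteeism has no pre-programme value, and T-transfer cannot provide one. The arm comparison remains valid; precision, a balance check and any before/after reading are lost.

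The gain from adding the value cannot be derived from the documents. A 9% to 25% fall in residual variance rests on an assumed partial correlation of 0.3 to 0.5 and a linear model. In a count model the gain would differ, and it could be smaller if prior-year VOC already carries much of the information. Absenteeism is one example of a social factor and one secondary outcome among several. The primary outcome and the total of 196 are untouched.

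**What to change.** In Table 2, mark school absenteeism at T-inclusion for both patient and parent. Ask it before randomisation, since the trial is open-label and the dyad is told its arm. Use a fixed look-back that matches the one used at T-transfer and T-24, with the same informants. In the Statistical analysis plan section, name this value as a covariate in the model for absenteeism, alongside the minimisation factors.

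The cost is one short self-declared item for patient and parent at a visit that already carries several questionnaires, plus one covariate. The drawback is that patients already enrolled would have to answer retrospectively, knowing their arm, or would lack the value; the analysis should say how such cases are handled.
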